#### Intervention fidelity

2.5.3

Fidelity monitoring will be conducted by the principal investigator throughout the trial. Given the sensitive and confidential nature of the psychoeducational sessions, audio or video recording will not be used; instead, fidelity will be assessed through two complementary methods. First, each delivering midwife will complete a structured session log immediately after every session, documenting delivery of required content elements, techniques used, and any deviations from the protocol. Second, the principal investigator will conduct individual supervision meetings with each delivering midwife, during which session logs will be reviewed against a structured fidelity checklist operationalising the objectives and key activities defined in Table 1. Acceptable adherence is defined as completion of ≥80% of required content elements per session. If adherence falls below this threshold, the midwife will receive structured feedback and, where necessary, booster training before continuing delivery. All protocol deviations will be recorded and reported in the final manuscript.

#### Criteria for discontinuing or modifying the intervention

2.5.4

The intervention may be discontinued or modified for an individual participant in the following circumstances: withdrawal of informed consent at any point during the trial; emergence of a severe psychiatric condition requiring specialist treatment (e.g., acute psychosis, severe depressive episode); clinically significant deterioration in psychological wellbeing as assessed by the delivering midwife and confirmed by the principal investigator; initiation of pharmacological treatment for anxiety or depression during the trial period; obstetric complications requiring hospitalisation or precluding participation; preterm birth prior to completion of the intervention; or inability to continue participation due to unforeseen personal circumstances.

In cases of discontinuation, the participant will be referred to appropriate clinical or psychological services where indicated. All outcome data collected prior to discontinuation will be retained and included in the intention-to-treat analysis. Participants who discontinue the intervention but remain willing to complete follow-up assessments will be encouraged to do so.

#### Strategies to improve adherence and monitoring of adherence

2.5.5

Adherence will be supported through flexible scheduling in person or via secure video conferencing, provision of written session summaries and educational materials after each meeting, reminder messages prior to scheduled sessions, and telephone or message contact between sessions to maintain engagement. Partner or family involvement is encouraged where appropriate. Adherence will be monitored via a standardised session log maintained by the delivering midwife, recording the number, duration, and format of completed sessions. For the per-protocol analysis, adequate adherence is defined as completion of at least four of the six planned sessions. Reasons for non-attendance or early discontinuation will be recorded and reported.

#### Concomitant care

2.5.6

Participants in both groups will continue to receive all routine antenatal care throughout the trial period. No concomitant structured psychological interventions or pharmacological treatments for anxiety or depression are permitted, as these constitute exclusion criteria. Use of other antenatal education resources, such as childbirth preparation classes or online informational materials, is not restricted but will be recorded at each follow-up assessment to allow for adjustment in sensitivity analyses.

The authors acknowledge that the multi-centre, multi-channel recruitment strategy—particularly the use of social media platforms and parenting forums—introduces a risk of contamination. Control participants may come into contact with intervention participants through the same online channels and consequently seek out psychoeducational support independently. This could result in an underestimation of the intervention effect. To minimise this risk, all participants will be asked at enrolment not to discuss study details with other enrolled women. At each data collection time point, control group participants will be asked whether they have used any form of psychological or psychoeducational support beyond standard antenatal care; this information will be recorded and included as a potential confounding variable in a sensitivity analysis.

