#### Control group

2.5.1

Women in the control group will receive standard antenatal care as is typical in Poland, comprising: antenatal education in accordance with the Polish Organizational Standard of Perinatal Care (46), covering pregnancy, childbirth, puerperium and social support; routine obstetric appointments and ultrasound examinations; and hospital care during and after childbirth provided by designated hospital staff. In addition, women in the control group will receive an informational booklet on preparing for childbirth, developed specifically for this trial by midwives from the research team. The booklet covers key topics including the physiology of labour and birth, pain management options, hospital admission procedures, postpartum care, and newborn care. It is designed to provide factual information without therapeutic or psychoeducational components, thereby serving as a minimal active control condition that addresses ethical concerns while maintaining a meaningful contrast with the intervention.

Although standard antenatal education in Poland covers some overlapping topics (e.g., childbirth physiology), it is delivered in a group format without individualised psychological assessment or anxiety-focused components. The intervention differs fundamentally in being individually tailored to each participant’s anxiety profile and grounded in a structured therapeutic framework. To monitor the integrity of the control condition, participants will be asked at each follow-up assessment to report the content and format of antenatal education received; this information will be recorded and included as a covariate in sensitivity analyses if meaningful variability is identified.

Potential contamination between groups is addressed in detail in the Concomitant Care section, including measures to minimise cross-group communication and a planned sensitivity analysis.

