*Session 3*: Methods of pain relief and stress management techniques is aimed at familiarising the patient with pharmacological and non-pharmacological methods of pain relief and teaching relaxation techniques. The midwife begins by explaining the physiology of labour pain and its role in the birthing process. She then presents non-pharmacological methods, such as breathing exercises, relaxation techniques, massages, labour positions, hydrotherapy or transcutaneous electrical nerve stimulation. Pharmacological methods are also discussed, including epidural anaesthesia, nitrous oxide and opioid medications, explaining their indications, benefits and potential limitations in detail. In the practical part, breathing and relaxation techniques are practised together with the patient; a companion may participate in the session at the patient’s request. At the end, the patient receives materials such as breathing exercise instructions, a list of pain relief methods and relaxation recordings. Partner participation will be documented in the session log and included as a covariate in sensitivity analyses if the frequency of attendance proves meaningful.

*Session 4*: Birth plan and communication with medical staff is focused on developing an individual birth plan and enhancing assertive communication skills with medical staff. The midwife introduces the concept of a birth plan as a document expressing the patient’s preferences and expectations regarding childbirth—for example, regarding labour positions, pain relief methods, the presence of a companion and skin-to-skin contact after birth. Together with the patient, she completes a birth plan form, discussing each option and providing objective information. The second part of the session is communication training—the midwife teaches the patient how to express her needs, ask questions and communicate assertively with the healthcare team. Specific phrases and conversation scenarios are practised, and the patient receives supporting materials, such as the completed birth plan, a leaflet on patient rights and a list of helpful questions for the staff.

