
#### Time II—post-intervention assessment

2.12.2

The second phase of data collection will consist solely of a follow-up measurement using the PRAQ-R2 to assess changes in the primary outcome.

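### Two planned sensitivity analyses adjust for post-randomisation variables that exist in one arm only, so they cannot separate contamination from self-selection

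*Protocol article*

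**What the plan says.** Section 2.5.6 (Concomitant care) acknowledges a contamination risk: "Control participants may come into contact with intervention participants through the same online channels and consequently seek out psychoeducational support independently". To deal with it, "control group participants will be asked whether they have used any form of psychological or psychoeducational support beyond standard antenatal care" at every data collection, and the answer is to be "included as a potential confounding variable in a sensitivity analysis". No condition is attached.

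Section 2.5.2 (Intervention, Session 3) adds: "Partner participation will be documented in the session log and included as a covariate in sensitivity analyses if the frequency of attendance proves meaningful".

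Two further adjustments concern antenatal education. Section 2.5.1 (Control group) asks participants at every follow-up what education they received; "this information will be recorded and included as a covariate in sensitivity analyses if meaningful variability is identified". Section 2.5.6 says that use of other education resources "is not restricted but will be recorded at each follow-up assessment to allow for adjustment in sensitivity analyses".

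On timing, section 2.12.2 states: "The second phase of data collection will consist solely of a follow-up measurement using the PRAQ-R2". Table 2 agrees and shows no other questionnaire at Time II.

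Section 2.14 sets the primary analysis as ANCOVA with group, baseline PRAQ-R2 and any stratification variables. It lists two pre-specified sensitivity analyses: one with midwife as a random effect, and a repeated-measures model for incomplete data. Neither is a contamination or partner adjustment.

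**The concern.** A confounder of a between-arm comparison must vary in both arms and must not be a consequence of allocation. Outside support, as section 2.5.6 describes it, follows from contact with intervention participants, so it arises after allocation, and only controls are asked about it. Partner attendance at a session can occur only where there are sessions, and section 2.5.5 encourages partner involvement as part of delivery.

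A covariate that is constant in one arm carries no information about imbalance between arms. Entering it removes the users from the comparison and leaves a self-selected remainder of one arm set against the whole of the other.

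What is at stake is interpretation. The outside-support analysis is offered as a check on whether contamination diluted the result. If it gives a larger or smaller effect than the primary analysis, the reader cannot tell whether that reflects contamination or the kind of woman who seeks support.

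**Working it through.** **Inputs from the protocol article.** Planned effect 3.27 points, 31 per group for 80% power, 37 per group recruited (section 2.9). Outside support recorded in controls only (2.5.6). Partner participation recorded in the session log only (2.5.2).

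**Inputs assumed.** p, the share of women in the affected arm with the variable present, from 0.1 to 0.4. D, the baseline-adjusted difference in Time II PRAQ-R2 between users and non-users, from -3 to +3 points. The document gives neither. It also gives no figure for these analyses, so there is none to reproduce.

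**Step 1: what the group coefficient becomes.** Let T = 1 for intervention, and X = 1 for outside support, with X = 0 for every intervention woman. Leaving baseline aside, the model with T and X has three cells and fits each cell mean exactly:

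- adjusted coefficient = mean(all intervention) - mean(control non-users)
- randomised difference = mean(all intervention) - [(1 - p) × mean(control non-users) + p × mean(control users)]
- adjusted - randomised = p × D

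For partner attendance, X = 0 for every control. The coefficient is mean(unaccompanied intervention) - mean(all controls), and the shift is -p × D.

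In one simulated data set the adjusted coefficient and the difference in means without the control users were both -0.0649, against a full-arm difference of 0.5187.

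**Step 2: with baseline in the model.** Simulation used 37 per arm, 3,000 runs per scenario, ANCOVA with baseline, an effect of -3.27 and a residual SD of 4.52. That SD is the one at which 31 per group gives 80% power: the detectable standardised difference at n = 31 is 0.723, and 3.27 / 0.723 = 4.52. The p × D shift does not depend on it. Adjusting for X and deleting the users agreed on average to within 0.01 in every scenario.

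Outside support, if it has no effect of its own (formula -3.27 + p × D; simulated mean in brackets):

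| p | D = +3 | D = 0 | D = -3 |
|---|---|---|---|
| 0.1 | -2.97 (-2.96) | -3.27 (-3.28) | -3.57 (-3.54) |
| 0.2 | -2.67 (-2.66) | -3.27 (-3.28) | -3.87 (-3.87) |
| 0.3 | -2.37 (-2.36) | -3.27 (-3.25) | -4.17 (-4.18) |
| 0.4 | -2.07 (-2.09) | -3.27 (-3.30) | -4.47 (-4.48) |

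At |D| = 3 the shift runs from 0.3 to 1.2 points, or 9% to 37% of 3.27. At D = 0 nothing moves, but at p = 0.3 the standard error rises from 1.07 to 1.17.

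Partner attendance at p = 0.3 (formula -3.27 - p × D): D = +3 gives -4.17 (simulated -4.15), and D = -3 gives -2.37 (simulated -2.36).

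**Step 3: selection and contamination are mixed.** D is the sum of how users differ anyway and what the support does. Take p = 0.3, a support effect of -2 and an uncontaminated effect of -3.27. Contamination pulls the randomised estimate to -3.27 + 0.3 × 2 = -2.67.

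- No selection: D = -2, adjusted = -2.67 - 0.6 = -3.27 (simulated -3.23). The adjustment recovers the uncontaminated effect.
- Users 3 points higher anyway: D = +1, adjusted = -2.67 + 0.3 = -2.37 (simulated -2.39). The adjustment moves away from it, although contamination is real.

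A D of +1 would look the same with selection of +1 and no effect of support at all.

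**Step 4: missing instead of zero.** Intervention women are not asked about support. If their value is left missing, a complete-case model drops that arm and no group effect can be estimated.

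**Step 5: timing.** Baseline questionnaires precede allocation (sections 2.10 and 2.11), so no control group exists to be asked then. Time II holds only the PRAQ-R2 (2.12.2, Table 2). As written, that leaves Time III, six weeks or more after delivery and after the primary endpoint. The education items promised at every follow-up meet the same obstacle at Time II.

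**The case against.** The strongest reply is that the primary analysis cannot move. Section 2.14 fixes it without any post-randomisation covariate, and no decision rule depends on the sensitivity analyses. That stands. A reader might infer that the trial's main result is biased; the document does not support this.

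A reader might also infer that every planned covariate of this kind is one-sided. The education items are put to participants generally, or in a paragraph that opens by referring to both groups, so they appear to be recorded in both arms. They are post-randomisation, but the one-arm argument does not reach them.

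Third, bias is a risk and not a certainty. If seeking support were unrelated to prognosis given baseline, the adjusted figure would approximate the uncontaminated effect, as Step 3 shows. That is fair. But women who seek support are self-selected, and nothing planned would test the assumption. A difference of 3 points is also sizeable, about 0.66 of the assumed residual SD (3 / 4.52), so the tabulated shifts are illustrations and not forecasts.

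Fourth, the model form is not spelled out, and partner attendance could be meant for an analysis within the intervention arm. The point is therefore conditional on a between-arm model. For outside support that is the natural reading of a variable called a potential confounder.

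Finally, the absence of a threshold for when variability or attendance counts as meaningful is detail that a separate analysis plan commonly holds. It is not counted here.

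**Conclusion.** The point holds in limited form. Outside support (unconditional) and partner participation (conditional) exist in one arm only. As covariates in a between-arm model they replace the randomised comparison with one that omits self-selected women from one arm. The shift is p × D for outside support and -p × D for partner attendance, in either direction and of unknown size; every p and D above is an assumption. It would be wrong to conclude that the benefit is necessarily understated, since the sign of D is not known.

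The primary ANCOVA is unaffected. What fails is the purpose of the outside-support analysis: it cannot separate contamination from self-selection. The conflict over what Time II collects is plain on the page and needs no assumption. Together these warrant a correction before data collection, but they do not threaten the main result.

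**What to change.** 1. Ask both arms the same outside-support and antenatal-education items at Time II and Time III, amend section 2.12.2 and Table 2 to include them, and report the answers by arm.
2. Do not enter outside support or partner attendance as covariates in the between-arm model. Describe partner attendance within the intervention arm only.
3. Limit covariate-adjusted sensitivity analyses of the treatment effect to pre-randomisation variables, such as recruitment source, which section 2.10 already records.
4. Reconcile sections 2.5.1, 2.5.2 and 2.5.6 with the two sensitivity analyses listed in section 2.14.
5. Treat any contamination-adjusted estimate as optional. It should preserve the randomised comparison and state its estimand and assumptions. Dividing the randomised effect by the between-arm difference in exposure is not a ready answer: it would treat any outside support as equivalent to the midwife sessions and would need an exclusion restriction.

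The cost is a few extra online items at Time II, slightly more burden for participants, and a minor amendment.

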### Outcomes

2.6

#### Primary outcome

2.6.1

The primary outcome is the levels of PrA, measured using the total score and three subscale scores of the Polish adaptation of the PRAQ-R2 (26). The total score ranges from 10 to 50 points. The three subscales are: Fear of Giving Birth (items 1, 2, 6; range 3–15), Worries about Bearing a Handicapped Child (items 4, 9, 10, 11; range 4–20), and Concerns about Appearance (items 3, 5, 7; range 3–15). The analysis metric is the change in total and subscale scores from baseline (Time I) to post-intervention assessment (Time II, 34–37 weeks of gestation), expressed as continuous variables. The method of aggregation is the mean score compared between groups.

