#### Secondary outcomes

2.6.2

Anxiety and depressive symptoms will be assessed using the PHQ-4 total score (range 0–12) and two subscale scores: PHQ-2 for depressive symptoms (items 1–2; cut-off ≥3) and GAD-2 for anxiety symptoms (items 3–4; cut-off ≥3). The metric is the change from baseline (Time I) to postpartum assessment (Time III, ≥6 weeks postpartum), with mean scores compared between groups.

Childbirth-related PTSD symptoms will be assessed prenatally using the PTSD-8 total score (range 0–24; no universally established cut-off in the original instrument) at baseline (Time I), and postnatally using the PPQ-II total score and subscale scores at Time III. Mean final values will be compared between groups.

Childbirth satisfaction will be measured using the BSS-R total score at Time III, with mean final values compared between groups.

Perceived social support will be assessed using the MSPSS total score (range 12–84) and three subscale scores (Significant Other, Family, Friends; range 4–28 each) at baseline (Time I) and postpartum (Time III), with mean scores compared between groups.

Infant feeding attitudes will be measured using the IIFAS total score at baseline (Time I) and reported descriptively.

Mode of birth and obstetric outcomes will be collected via the Custom Postpartum Questionnaire (Part B) at Time III and reported as frequencies and proportions.

Although all instruments will be administered in full, not all subscales or total scores will be analysed within the scope of this trial; some data will be reserved for secondary research questions and future analyses. Detailed descriptions of all measurement instruments, including psychometric properties of Polish adaptations, are provided in section 2.12 Data Collection Methods. Formal permissions for the use of all Polish adaptations have been obtained from the respective copyright holders prior to the commencement of the study.

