### Sample characteristics and size

2.9

Sample size planning was informed by the Polish validation study of the PRAQ-R2, from which an anticipated 10% reduction in the mean score (3.27 points) and variability estimates for repeated measurements were derived. In this two-group randomised trial, the primary comparison will be the between-group difference in post-intervention PRAQ-R2 adjusted for baseline score, analysed using a two-sided significance level (*α*) of 0.05. Based on these assumptions, G*Power 3.1 indicated a minimum of 31 participants per group to achieve 80% statistical power. It should be noted that no MCID has been established for the PRAQ-R2 (26, 38). The 3.27-point planning assumption was derived from 10% of the Polish normative mean and additionally verified against distribution-based criteria: the anticipated difference approximates 0.5 SD of the total score [SD ≈ 8.56; (38)], a widely accepted proxy for minimal important difference in the absence of anchor-based estimates. This limitation is acknowledged; the present trial will contribute effect size data to inform future MCID derivation.

Because this is the first evaluation of an intensive, individually delivered midwife-led psychoeducational intervention in this setting, the final recruitment target of 74 women (37 per group) was retained as a pragmatic sample size balancing methodological considerations and intervention deliverability. The study is intended to provide an initial estimate of treatment effect and variance, and to inform the design of a future larger trial. An additional 20% was incorporated into the recruitment target to account for anticipated dropout, loss to follow-up, and incomplete outcome data (52, 53).

To achieve this, approximately 500 women will be screened in the second trimester to identify the eligible cohort with elevated PRAQ-R2 scores. This estimate reflects the expected prevalence of elevated PrA in the target population—a Polish pilot study found that approximately 56% of low-risk pregnant women scored ≥30 points on the PRAQ-R2 (26), combined with additional attrition anticipated from non-response, incomplete questionnaire completion, failure to meet remaining eligibility criteria, and non-consent prior to randomisation. Sample size planning was performed using G*Power 3.1.

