### Statistical analysis plan

2.14

Analyses will be conducted according to randomised group allocation and will primarily follow the intention-to-treat principle, insofar as outcome data are available. The primary endpoint is PrA measured using the PRAQ-R2 at 34–37 weeks’ gestation. The primary analysis will compare post-intervention PRAQ-R2 scores between groups using analysis of covariance (ANCOVA), with treatment group as the main factor and baseline PRAQ-R2 score as a covariate. The primary outcome is assessed at two prenatal time points only: baseline and post-intervention. The postpartum assessment applies exclusively to secondary outcomes.

Secondary outcomes will be analysed using regression models appropriate to outcome type, with logistic regression for binary outcomes and linear regression for continuous outcomes. Secondary analyses will be considered supportive and exploratory; no formal adjustment for multiplicity is planned. Missing data will be described by study arm and time point. The primary analysis assumes data are missing at random (MAR); this assumption will be examined via sensitivity analysis, using a mixed-effects model for repeated measures applied to all available longitudinal data. Multiple imputation is not planned. The possibility of data missing not at random (MNAR) cannot be excluded and is acknowledged as a limitation. Stratification variables included in the randomisation will be entered as covariates in the primary ANCOVA model. A supportive per-protocol analysis will also be conducted among participants with observed primary endpoint data; in the intervention arm, this will additionally require completion of at least four intervention sessions. Two pre-specified sensitivity analyses will be conducted: (1) a linear mixed-effects model including midwife as a random effect, to account for potential clustering by intervention deliverer; and (2) a mixed-effects model for repeated measures applied to all available longitudinal data under a missing-at-random assumption, to assess the robustness of findings in the presence of incomplete data.

The mode of intervention delivery (in-person versus remote) will be recorded. As the trial is not powered for formal moderator analyses, any comparison by delivery mode will be considered exploratory and interpreted cautiously.

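### Section 2.6.1 names four PRAQ-R2 scores as the primary outcome without hierarchy, while 2.9 and 2.14 describe one baseline-adjusted comparison; the total score should be named as sole primary endpoint

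*Protocol article*

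**What the plan says.** Three places in the protocol article define the primary outcome or its analysis.

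- **Section 2.6.1 (Primary outcome):** "The primary outcome is the levels of PrA, measured using the total score and three subscale scores of the Polish adaptation of the PRAQ-R2". On the scale of measurement: "The analysis metric is the change in total and subscale scores from baseline (Time I) to post-intervention assessment". On the summary: "The method of aggregation is the mean score compared between groups". No covariate is named, and the four scores are not ranked.
- **Section 2.9 (Sample characteristics and size):** "the primary comparison will be the between-group difference in post-intervention PRAQ-R2 adjusted for baseline score", at two-sided alpha 0.05. The planning difference of 3.27 points is compared with an SD of about 8.56 for the total score.
- **Section 2.14 (Statistical analysis plan):** "The primary analysis will compare post-intervention PRAQ-R2 scores between groups using analysis of covariance (ANCOVA"), with "baseline PRAQ-R2 score as a covariate". The section does not say whether this means the total score only.

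The one sentence on multiplicity, in 2.14, says that no formal adjustment is planned; it concerns secondary analyses, which are declared supportive and exploratory. H1 (section 1.3) is worded in terms of levels of pregnancy-related anxiety, the same general term that 2.6.1 attaches to all four scores.

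**The concern.** The sections differ on how many variables are primary (four or one) and on the metric (change or baseline-adjusted final score). No rule says what happens if the scores disagree. Read literally, 2.6.1 would let a difference on one subscale alone, for example concerns about appearance, be reported as meeting the primary outcome while the total score shows nothing. The Discussion attaches policy consequences both to a positive and to a null result, so what counts as positive needs to be fixed before outcome data are seen.

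This cannot be left to a document not shown. The section headed Protocol and statistical analysis plan says that both are published in full within this article, and the conflict is between statements that it makes.

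**Working it through.** **1. The plan's own figure.** Section 2.9 gives 31 per group for 80% power. For one baseline-adjusted comparison,

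n per group = 2(z₀.₉₇₅ + z₀.₈₀)² · SD²(1 − ρ²) / Δ²,

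with Δ = 3.27 and SD = 8.56 (2.9), and ρ the baseline-to-follow-up correlation. With ρ = 0 this is 2 × 7.849 × 73.27 / 10.69 = 107.6, so 108. It reaches 31 when 1 − ρ² is about 0.288, so ρ is about 0.844. The article does not print ρ, so 31 cannot be confirmed from it. That is a missing input and a separate matter. What matters here is that the printed inputs describe one comparison of the total score.

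**2. False-positive rate if any of the four scores may count.** Four tests at 0.05 have an upper bound of 4 × 0.05 = 0.20. If independent, they give 1 − 0.95⁴ = 0.185. The total is the sum of its subscales, so the tests are correlated. A null simulation (400,000 draws) took three subscale test statistics with common correlation r, plus a total weighted 3:4:3 by the item counts in 2.6.1:

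| r (assumed) | Any of four, two-sided 5% | Any of four, favourable direction (nominal 2.5%) |
|---|---|---|
| 0 | 16.1% | 8.2% |
| 0.3 | 14.4% | 7.3% |
| 0.5 | 13.0% | 6.5% |
| 0.7 | 11.0% | 5.5% |

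**3. Does the change metric add a route?** Write the ANCOVA of the final score as Y₁ = a + τG + bY₀ + e. Subtracting Y₀ gives Y₁ − Y₀ = a + τG + (b − 1)Y₀ + e. The treatment effect τ, its standard error and its p-value are identical. With baseline as covariate, change and final score are therefore the same test. They differ only if raw mean changes are compared without the covariate, which the wording of 2.6.1 allows but does not prescribe. In that case the two test statistics correlate at √((1 + ρ)/2). Accepting the total score on either one gives 6.3% (ρ = 0.84) to 7.8% (ρ = 0.3). Four scores on both metrics give about 16% to 21%, for r of 0.3 to 0.5 and the same range of ρ.

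**4. Could four primaries be kept?** A Bonferroni split gives 0.05/4 = 0.0125 each. At ρ = 0.844 and 31 per group, power for the total score is Φ(2.802 − 2.498) = Φ(0.304), about 0.62 instead of 0.80. Restoring 80% needs about 31 × (2.498 + 0.842)² / (1.960 + 0.842)² = 31 × 11.15/7.85, or about 44 per group before dropout. The trial is not sized for four primary scores.

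**The case against.** The best defence is that 2.9 and 2.14 already settle the matter. Section 2.9 speaks of one primary comparison at one alpha and checks its difference against the SD of the total score; 2.14 refers to a single baseline score. On that reading 2.6.1 is merely loose: it describes what is measured, not what is tested. No passage says that success on any one score is enough, and H1 is directional, so a false claim of benefit is better described by 5.5% to 8.2% against 2.5% than by the two-sided figures.

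Much of this stands. It would be too strong to say that the trial has no error control, because one alpha is set for one described comparison. But the defence rests on inference. Neither 2.9 nor 2.14 says that only the total is primary, and 2.6.1, which defines the outcome, says otherwise in plain terms.

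A reader might also infer more from section 2.6.2, which uses different metrics for different instruments: "The metric is the change from baseline (Time I) to postpartum assessment" for PHQ-4 and "Mean final values will be compared between groups" for the PTSD measures. The documents do not support the stronger readings:

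- **Secondary scores as further routes to a positive primary result.** Section 2.14 declares secondary analyses supportive and exploratory.
- **Secondary scores compared without baseline adjustment, against 2.14.** The ANCOVA in 2.14 is specified for the primary analysis. For continuous secondary outcomes 2.14 prescribes linear regression and neither lists nor excludes covariates.
- **A fixed loss of precision.** The variance ratio against ANCOVA is 2/(1 + ρ) for change and 1/(1 − ρ²) for unadjusted final values. Both equal 1.33 only at ρ = 0.5; at 0.3 they are 1.54 and 1.10, at 0.7 they are 1.18 and 1.96. No general figure follows.
- **PPQ-II analysed on the wrong metric.** It is measured only at Time III, so final values are all there is. Adjusting it for a different baseline instrument would be a preference, not a correction.

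**Conclusion.** The point holds for the primary outcome. Section 2.6.1 contradicts 2.9 and 2.14 on the number of primary scores and, as worded, on the metric, and no rule covers the four scores. The inflation in step 2 of the working is conditional: it arises only if a significant result on any of the four scores may be taken as support for H1, which the text permits but does not state. It also rests on assumed inter-subscale correlations. The metric adds little unless raw mean changes are tested. The point does not extend to the secondary outcomes.

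**What to change.** Before outcome data are seen:

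1. In 2.6.1 and 2.14, name the PRAQ-R2 total score at Time II (34–37 weeks), compared between groups by ANCOVA adjusted for baseline total score, as the sole primary endpoint. With one test, the primary error rate is 5%.
2. In 2.6.1, replace the change-score metric and the comparison of means with this definition.
3. Move the three subscales to the secondary, exploratory outcomes, each by ANCOVA on its own baseline.

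Optional and minor: state in 2.14 that the Time III linear regressions for PHQ-4 and MSPSS include their own baseline as covariate. The article is silent on this, and both baselines are already in the schedule.

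The cost is wording, handled through the route that the Ethics section sets for important amendments. The subscales lose primary status. The sample size does not change, and no new data or visits are needed.
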